#### Young person/parent interviews

Twenty young people participating in the RCT (10 per arm) will be invited to take part in in-depth interviews after their final assessments (23-week assessment). A separate interview will be undertaken with a parent/carer (all parents whose child participates will be invited). These parents/carers will complete a separate consent form for this interview. The research practitioner will have ongoing dialogue with parents/carers about their potential participation in the interviews during the follow-up visits. Participation in the interviews will be ascertained at the final research assessment. Participants will be asked about their experience and views of the process of accessing help, the content of sessions, contacts had in addition to study therapy sessions, how they feel they have benefitted or not from receiving the intervention, the experience of ending therapy and suggestions for improvement.

As with all clinical trials, there remains the possibility for some participants to withdraw from the study. There is a process in place to accurately record participant withdrawals/dropouts from the study. It will be established whether participants withdraw from the therapy (either IPC-A or TAU) and/or from the whole trial. Those who withdraw from therapy only will be followed up and invited to participate in the process evaluation interviews, while those who withdraw from the whole trial will be lost to follow-up and interviews.

#### Staff focus groups

Following completion of delivery of the IPC-A and TAU arms, focus groups will take place in participating services to understand staff perspectives of each study arm. These will be separate for IPC and TAU therapists. For IPC-A therapists, discussion will focus on barriers and facilitators to successful delivery, experiences and views of intervention sessions, additional work required to support delivery of IPC and suggestions for improvement. For TAU therapists, discussion will focus on how TAU is delivered, the additional support YP in TAU have received and their awareness and perspectives of IPC-A.

#### Focus group with professional stakeholders

At the end of the study, an additional focus group will be conducted with commissioners, education representatives and service managers to review study findings and discuss implementation barriers and sustainability of implementation.

#### Site profile questionnaires

Questionnaires at the beginning and end of study will aim to understand the broader service context in which the intervention is delivered, including TAU for young people with mental health needs; policies, protocols and procedures used by staff; numbers of YP with mental health needs and proportion with depression; training and experience of staff in treating depression in YP; and allocation and distribution of staff to support YP with mental health needs.

### Analysis

#### Statistical

Recruitment and retention rates will be estimated with 95% confidence intervals (CIs). Assuming sufficient information, time until drop-out will be analysed using ‘time-to-event’ methods, i.e. in an effort to identify baseline factors likely to be related to drop-out. The proposed primary outcome measure for the definitive RCT is the RCADS depression score at 10 weeks. Although the proposed study is not designed to assess efficacy, the mean between-group difference will be estimated using a general linear model including baseline RCADS depression score and treating therapist as a random effect. A 95% CI will be constructed to assess whether the treatment benefit is feasibly greater than the minimal clinically significant difference, i.e. whether or not it is included within the CI. A similar approach will be undertaken for the secondary outcome measures. The rate of completion of each outcome measure will be reported. If appropriate, depending on the proportion of missing values, multiple imputation will be undertaken and between-group differences re-estimated as a sensitivity analysis. Further parameters, such as within group variation, needed for the design of a subsequent full-scale trial, will also be estimated. All statistical analysis will be undertaken using STATA.

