### Sample size

Sixty eligible young people will be randomised all together. The sample size is not based upon estimation of efficacy but is in keeping with published suggestions [29] and believed to be practically possible within the limits of the project. Further, it should enable us to assess rates of recruitment and retention to a reasonable degree of precision; assuming an attrition rate of around 20%, a sample of 60 would provide an estimate with 95% confidence interval of width 20% (i.e. +/− 10%). For a recruitment rate of around 50%, the interval width would be around 25% (i.e. +/− 12.5%).

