### Randomisation

Randomisation will be coordinated remotely by the Norwich Clinical Trials Unit (CTU). Participants will be randomised in a 1:1 allocation ratio, using a stochastic minimisation algorithm to minimise imbalance between groups in baseline symptom severity, gender and study site. Allocation will be managed by the Data Management Team at Norwich CTU via a web-based system; it will not be accessible by anyone outside of this team, including the research team, trial therapists and participants; thus, allocation concealment will be maintained.

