### Data collection

#### Outcome measures

Participants will be assessed at baseline (pre-randomisation) and followed up at 10 weeks and 23 weeks, with an additional 5-week follow-up (online with telephone support). The following outcome measures will be used: demographic characteristics of young person; Kiddie Schedule for Affective Disorders and Schizophrenia (K-SADS) depression section to assess for presence of DSM depressive disorders [30, 31]; Revised Children’s Anxiety and Depression Scale (RCADS) to assess self-rated severity of symptoms across depression, anxiety disorders and OCD [32]; Family Assessment Device (FAD) to measure quality of family relationships of participants [33]; Cambridge Friendships Questionnaire (CFQ), which measures quality of peer relationships of participants [34]; Employment, Education or Training in previous 4 weeks (NEET status), to capture levels of inactivity amongst young people who are not in work, education or training; Short Warwick-Edinburgh Mental Wellbeing Scale, which will measure mental wellbeing [29]; Modified Client Service Receipt Inventory (Modified CSRI), which will record information on service utilisation, income, accommodation and other cost-related variables [35]; and Health-related quality of life measured using the Child Health Utility 9D (CHU9D) [36].

The RCADS [32], FAD [33] and CFQ [34] will be repeated at an online week 5-follow-up. All outcome measures will be repeated at week 10 and 23 follow-up except for demographic characteristics of young person and the K-SADS depression section. Information about gender of therapist, attendance/non-attendance at planned therapy sessions and location of sessions will be collected by therapists in both treatment arms.

Table 1 shows the schedule of enrolment, interventions and assessments in accordance with the SPIRIT guidelines.

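### The week-5 RCADS depression score is collected but plays no part in the main week-10 estimate, which can be biased if loss to follow-up tracks early response differently in the two arms

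*Protocol article*

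**What the plan says.** Under Outcome measures, the RCADS and two other questionnaires "will be repeated at an online week 5-follow-up", and, with stated exceptions that do not include RCADS, "All outcome measures will be repeated at week 10 and 23 follow-up". RCADS depression is therefore available at baseline and at weeks 5, 10 and 23.

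The Statistical section names the week-10 RCADS depression score as the proposed primary outcome of the definitive trial. For this study, "the mean between-group difference will be estimated using a general linear model including baseline RCADS depression score", with therapist as a random effect. The 95% interval is then compared with the smallest difference regarded as clinically important. On missing data it says: "If appropriate, depending on the proportion of missing values, multiple imputation will be undertaken", as a sensitivity analysis. It does not name the imputation variables. A time-to-event analysis of drop-out looks for baseline predictors only.

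The estimate has two uses. Aims and objectives asks whether the interval for post-treatment benefit includes a clinically significant effect. Progression criteria lists a 3-point difference in week-10 means as one of six criteria that the steering committee weighs.

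**The concern.** A linear model for the week-10 score with baseline as its only RCADS covariate uses, by default, only people who have a week-10 score. Among them, baseline adjustment does not correct for selection on what happened after baseline. If, for example, IPC-A participants who had not improved by week 5 were more likely to be lost and TAU losses were unrelated to response, the remaining IPC-A group would look better than the randomised group and the benefit would be overstated.

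The week-5 score carries information about exactly this and is collected in both arms. Participants know their allocation (Blinding) and the arms are treated by different staff (Control: treatment as usual), so loss that differs by arm is possible. At stake is a shift in the one efficacy-type figure taken forward. The confidence interval would not show that shift.

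**Working it through.** **1. The plan's own figures.** "Sixty eligible young people will be randomised all together" and "Participants will be randomised in a 1:1 allocation ratio", so 30 per arm. The stated precision is "assuming an attrition rate of around 20%, a sample of 60 would provide an estimate with 95% confidence interval of width 20" per cent, and "For a recruitment rate of around 50%, the interval width would be around 25% (i.e. +/− 12.5" per cent. Wald half-width = 1.96 × √(p(1 − p)/60):

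- p = 0.20: 1.96 × √(0.16/60) = 0.101, width 20.2%.
- p = 0.50: 1.96 × √(0.25/60) = 0.127, width 25.3%.

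Both figures are reproduced. The 20% is used there to illustrate precision. Separately, Progression criteria accepts 80% completion at week 10, so up to 0.20 × 60 = 12 people may be missing, which leaves 48, or 24 per arm if the loss is equal.

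**2. Assumptions not in the article.** SD 5 to 7. Correlations 0.6 (baseline to week 5), 0.5 (baseline to week 10) and 0.65 (week 5 to week 10). True benefit 3 points at week 10 and 1.5 at week 5. Where drop-out depends on response, its log-odds change by 1 per SD of week-5 change from baseline. Therapist effect omitted. Large-sample simulation (400,000 to 2,000,000 records per scenario) compared baseline-adjusted complete-case regression with imputation by arm from baseline and week 5.

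**3. Bias of the complete-case week-10 estimate, in points (range over SD 5 to 7).**

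| Drop-out pattern | 10% missing | 20% missing | 30% missing | Direction |
|---|---|---|---|---|
| Unrelated to response | about 0 | about 0 | about 0 | – |
| Same relation in both arms, equal rates | about 0 | about 0 | about 0 | – |
| IPC-A non-responders leave; TAU unrelated | 0.16–0.23 | 0.33–0.41 | 0.47–0.68 | overstates benefit |
| IPC-A responders leave; TAU unrelated | 0.16–0.27 | 0.31–0.43 | 0.45–0.62 | understates benefit |
| IPC-A non-responders and TAU responders leave | 0.32–0.46 | 0.60–0.86 | 0.93–1.30 | overstates benefit |

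A common mechanism with 20% missing overall, where rates differ only because responses differ, gives 0.05 to 0.14 towards no difference (week-5 benefit 1.5 or 3). Using week 5 brought the bias to within about 0.04 of zero in every row of the table.

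**4. Trial-sized check.** 30 per arm, SD 6, baseline correlations 0.5, week-5 to week-10 correlation 0.7, 18–20% missing, 4,000 replicates, true benefit 3. For random, IPC-A-only and opposite-direction drop-out:

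- Complete-case: 2.99, 3.43 and 3.84.
- Using week 5: 2.99, 3.01 and 2.97.

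Under random drop-out the standard error was 1.48 using week 5 against 1.54, a reduction of 1 − 1.48/1.54 = 4%. A further run with the same SD, correlations and sample size, but log-odds rising by 1 per SD of the week-5 score itself and 20–21% missing, gave complete-case means of 2.99, 3.50 and 4.00, against 3.00, 3.01 and 3.02. In that run's setting, with a true benefit of 1.5, the chance of a point estimate of at least 3 was 16%, 25% and 37% complete-case, against 15–16% using week 5.

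**5. Set against sampling error.** Half-width with 24 per arm, adjusted for baseline (r = 0.5) = 1.96 × SD × √(1 − 0.25) × √(2/24):

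- SD 5: 2.45
- SD 6: 2.94
- SD 7: 3.43

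With SE 1.54, the chance that a 95% interval includes the true value falls from 0.95 to Φ(1.96 − 0.43/1.54) − Φ(−1.96 − 0.43/1.54) = 0.941 for a bias of 0.43. For a bias of 0.84 it falls to 0.915 by the same formula.

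**The case against.** The case against is substantial. Analysis of covariance at the chosen time point, with multiple imputation as a sensitivity analysis, is a conventional plan. Imputation variables are commonly left to an analysis plan, which is not shown here. That disposes of any complaint that the article fails to name them. It does not dispose of the order the article itself fixes: the baseline-adjusted week-10 model is the main estimate, and imputation is conditional and secondary.

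A reader might infer several stronger things that the document does not support:

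- *That missing data are ignored.* They are not. Imputation, completion rates and a drop-out analysis are all planned, and the imputation could draw on week 5.
- *That the article restricts the model to those seen at week 10.* It does not say so. This is the default behaviour of such a model, and it fits with bringing missing values back only through imputation.
- *That stopping therapy early removes the outcome.* Young person/parent interviews states that people who leave therapy but not the trial continue to be followed up. Only whole-trial withdrawal or a missed assessment loses the score.
- *That the estimate is biased.* Material bias needs the link between loss and early response to differ by arm. The simulations assume that drop-out depends on week-5 response, so the success of conditioning on week 5 is built in. They do not cover missing week-5 scores, which are possible for an online assessment.
- *That progression relies on this figure.* It bears on one of six criteria, each weighed by how far it is met, and the Statistical section disclaims any aim of testing efficacy.

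**Conclusion.** The point holds as a worthwhile improvement, not as a demonstrated error. Week-5 RCADS is collected in both arms, and the main week-10 estimate as stated does not use it.

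At the 20% missingness the progression criteria tolerate, the bias is about 0.3 to 0.4 points if one arm is affected. It is 0.6 to 0.9 if the arms are affected in opposite directions (about 1.0 in one run with a different drop-out rule), and near zero if they behave alike. At 10% missing, these figures are roughly half. The larger values are not trivial against 3 points, but they are well inside the half-width of about 2.5 to 3.4. The interval question is therefore little affected, and the point-estimate criterion somewhat more so.

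Every bias figure rests on assumed SDs, correlations and drop-out patterns, with no therapist effect and complete week-5 scores.

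**What to change.** In the Statistical section, let the main week-10 between-group estimate use week-5 RCADS depression, by one of two routes chosen in advance:

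- **Repeated-measures mixed model** of the follow-up RCADS depression scores, with categorical visit, treatment-by-visit and baseline RCADS. Keep the planned therapist random effect and report the week-10 contrast. Categorical visit also absorbs any average shift from the online mode at week 5.
- **Multiple imputation**, if that model is judged too heavy for 60 participants. Use the planned week-10 model, therapist effect included, after imputation by arm with week-5 and week-23 RCADS as auxiliary variables. Make this the main analysis, no longer conditional on the proportion missing.

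Either way, report the complete-case week-10 model as the sensitivity analysis.

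The cost is a change of wording and a little programming, with no new data. The downsides are more parameters in a small sample and less gain where week-5 scores are missing too.

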## Aims and objectives

The ICALM study will inform a future trial of the effectiveness and cost-effectiveness of the intervention (IPC-A). The aim of the proposed research is to answer the following feasibility questions which arise from the variability in service models across providers of non-specialist mental health support for young people:
Are trial procedures, including recruitment (of participants and therapists), randomisation, research assessments and follow-up, feasible and acceptable to support the conduct of a future RCT?How are IPC-A and current treatment as usual (TAU) delivered and how and why does intervention delivery vary across differing service contexts?To what extent does contamination of the control arm occur and should it be mitigated against in a future trial?Does the interval estimate of benefit of IPC-A over TAU in depression scores at post-treatment include a clinically significant effect?

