### Progression criteria

#### Feasibility outcomes

The primary output of this feasibility trial will be the design of the subsequent full-scale trial. The TSC will assess the trial against the following criteria and make recommendations regarding the suitability of the proposed design for the full-scale trial, based on the extent to which these criteria are met.
Recruitment rate is at least 80% of targetAt least 70% of those randomised to receive the intervention attend at least three therapy sessions within the 10-week treatment windowFollow-up assessments are completed by at least 80% of participants at 10 weeks and 70% of participants at 23 weeksAt least 80% of IPC treatment sessions reviewed meet treatment fidelity criteriaContamination of the control arm can be sufficiently limited for individual randomisation to be justifiedThe mean RCADS depression scores of the IPC-A and TAU groups at 10 weeks are indicative of a clinically significant difference in depression (3 points)

The rate of completion of each outcome measure will be calculated and acceptability assessed via the process evaluation. We shall estimate the expected cost of the intervention and likely drivers of cost. The results of the feasibility study, the views of participants in the stakeholder focus group and guidelines from the Medical Research Council (MRC) on developing and evaluating complex interventions, will inform research design for subsequent research. If the proposed method is unable to limit contamination adequately, then a cluster trial or stepped wedge design will be considered. We will recommend an internal pilot study if outcomes from feasibility suggest that substantial changes to the protocol are required before progression. If the above criteria are met, we will apply for funding to progress to a multi-site, assessor-blind, RCT of the effectiveness and cost-effectiveness of IPC-A in comparison to TAU for adolescents presenting to non-specialist services with depressive symptoms, informed by our feasibility results.

Ultimately, if a future trial demonstrates IPC to be effective, an IPC-A training programme could be implemented nationally. This would facilitate rapid expansion of the therapy workforce, increasing access to evidence-based treatment for adolescent depression.

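### Gender and study site are used to allocate participants but are not named in the analysis model, so the 95% CI for the 10-week difference may be somewhat too wide (minor)

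*Protocol article*

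**What the plan says.** Under Randomisation, the protocol article allocates 1:1, "using a stochastic minimisation algorithm to minimise imbalance between groups in baseline symptom severity, gender and study site". Under Analysis, Statistical, it names the outcome ("The proposed primary outcome measure for the definitive RCT is the RCADS depression score at 10 weeks") and says that the mean difference will be "estimated using a general linear model including baseline RCADS depression score and treating therapist as a random effect". Secondary outcomes are to be handled in a similar way. One of the three allocation factors, severity, therefore enters the model through the baseline score. Gender and site are not mentioned there or anywhere else as model terms, and no reason is given for leaving them out.

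The interval has a stated use: "A 95% CI will be constructed to assess whether the treatment benefit is feasibly greater than the minimal clinically significant difference". Aims and objectives asks the same thing as a feasibility question: "Does the interval estimate of benefit of IPC-A over TAU in depression scores at post-treatment include a clinically significant effect". The same Statistical section says that parameters such as within-group variation will be estimated for the full trial.

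The progression criteria, under Feasibility outcomes, also refer to a clinically important difference. They require that the mean 10-week scores of the two groups "are indicative of a clinically significant difference in depression (3 points"). That wording is about means, not about the interval.

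**The concern.** Minimisation reduces chance imbalance in gender and site, so the treatment estimate varies less from trial to trial than under simple randomisation. A model without these factors leaves their variance in the error term and does not credit the estimate with the balance. If either factor is prognostic, the standard error overstates the real uncertainty.

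An over-wide interval is normally called conservative. Here it is lenient, because the question is whether the interval reaches a clinically significant benefit, and a wider interval reaches it more easily.

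The second thing at stake is the set of variances passed to the full trial. Practitioners are employed by local services in two counties, so a county difference that the model does not fit can appear as variation between therapists.

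**Working it through.** **The plan's own figures.** The only precision figures in the article are for proportions with n = 60 (Sample size). They reproduce:
- 20% attrition: 1.96 × √(0.20 × 0.80 / 60) = 10.1%, stated as ±10%.
- 50% recruitment: 1.96 × √(0.50 × 0.50 / 60) = 12.7%, stated as ±12.5%.

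This point changes neither. The article gives no precision figure for the RCADS difference.

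**Inputs from the article.** 60 randomised 1:1, about 20% attrition (48 analysed, 24 per arm), two counties, a difference of 3 points.

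**Assumed, because the article does not give them.** SD 5 (6 in a second set of runs), baseline-outcome correlation 0.5, minimisation probability 0.8, gender and site effects of 0 to 5 points each.

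**Closed-form check, no therapist term.** With SD 5, the residual variance after baseline adjustment is 25 × (1 − 0.5²) = 18.75. A two-level factor split evenly with effect d adds d²/4, so two such factors add d²/2 if they are left out. The half-width is t(45) × √(variance × 2/24), with t(45) = 2.014:
- d = 0: variance 18.75, half-width 2.52
- d = 2: variance 18.75 + 2 = 20.75, half-width 2.65
- d = 3: variance 18.75 + 4.5 = 23.25, half-width 2.80

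**Simulation of minimised trials, 48 analysed, no therapist term** (3000 runs per setting, SD 5). Mean half-widths in points:

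| Effect of each factor | Stated covariates | Plus gender and site |
|---|---|---|
| 0 | 2.52 | 2.55 |
| 1 | 2.56 | 2.55 |
| 2 | 2.64 | 2.54 |
| 3 | 2.80 | 2.55 |
| 5 | 3.22 | 2.54 |

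The mean error of the estimate is within 0.03 points under both models. Over runs with 60 or 48 analysed, coverage without the two factors is 94.5–95.2% at 0 to 1 point, 95.8–95.9% at 2, 95.8–96.5% at 3 and 97.9–98.1% at 5. With them it stays at 94.7–95.7%. The Monte Carlo standard error is √(0.95 × 0.05 / 3000) = 0.4 percentage points.

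The second set (SD 6, 4000 runs) gives full widths of 6.28 against 6.12 at 2 points (3% wider) and 6.54 against 6.12 at 3 points (7% wider).

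**With a therapist random intercept** (assumed three therapists per arm per site, true therapist variance 1.25, SD 5, about 400 runs per setting). Half-widths without and with gender and site:
- 0 points: 2.98 and 3.01
- 1 point: 2.97 and 2.94
- 2 points: 3.23 and 3.03 (3.23/3.03 = 1.07)
- 3 points: 3.50 and 2.97 (3.50/2.97 = 1.18)

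At 3 points the mean estimated therapist variance is 4.2 without the factors and 2.0 with them. The therapist term does not repair the omission. Many of these fits gave convergence warnings, so the figures are approximate.

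**Effect on the check.** The interval includes 3 when the estimate is within one half-width of 3. At 3-point effects with the therapist term, the smallest estimate whose interval still reaches 3 is 3 − 3.50 = −0.50 without the factors and 3 − 2.97 = 0.03 with them. The answer changes only for estimates in that band of about 0.5 points. Without the therapist term the band is 2.80 − 2.55 = 0.25 points, and at 2-point effects it is 2.64 − 2.54 = 0.10.

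**Effect on variance.** In the closed form, the residual variance rises by 20.75/18.75 = 1.11 at 2 points and 23.25/18.75 = 1.24 at 3 points.

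**The case against.** The strongest reply is that the covariate list is not closed. The article says the model includes baseline score, it condenses a longer protocol, and an unseen analysis plan may add terms. That stands in part and lowers confidence. But the article goes as far as naming a covariate and a random effect, and someone who followed it as written would leave out gender and site.

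The second reply is size, and it stands. The effect depends on prognostic strengths that the documents do not give, is nil at 0 to 1 point, and stays close to nominal coverage at 2 to 3 points without the therapist term. Minimisation here is stochastic and some participants will be lost, so balance is improved rather than guaranteed. The simulations allow for both.

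Three stronger readings are tempting and are not supported:
- A reader might infer that the 3-point progression criterion is distorted. It is worded on mean scores, and the estimated difference is unbiased with or without the two factors.
- A reader might take the section on the control arm as evidence that outcomes differ by county. It says county and team differences may contribute to variation in the usual-care options on offer, and says nothing of 10-week scores. If usual care did work differently by county, that would be a treatment-by-site difference, which a site main effect alone does not remove.
- A reader might infer that the full trial's sample size will be wrong. The article promises an estimate of within-group variation but does not say that it will be the residual SD of this model.

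**Conclusion.** The mismatch between allocation and analysis is real, and its consequence is minor. It causes no bias. If gender or site is prognostic, the interval in the Statistical section and in the aims is somewhat too wide, which makes its check easier to pass, and the residual and therapist variances may be inflated. Across the assumed SDs of 5 to 6, the widening is about 3 to 7% at 2 points per factor and about 7 to 18% at 3 points. The top of each range comes from the approximate therapist-model runs. For a feasibility trial of 60 that is not designed to assess efficacy, this is a refinement that costs almost nothing rather than a flaw that threatens the conclusions.

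**What to change.** In the Statistical section, state the 10-week RCADS model as: fixed effects for arm, baseline RCADS depression score, gender and study site (one indicator for the two counties), with therapist as a random effect. Add the same two terms to the secondary-outcome models. Report the residual and therapist variances from this model, and say that they assume the full trial will adjust for the same factors.

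The cost is one sentence and two degrees of freedom. If neither factor is prognostic, the half-width grows by 2.55 − 2.52 = 0.03 points. Both variables are already recorded for randomisation. If the analysis plan already includes these terms, the article's description only needs to be brought into line with it.

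### The test of benefit against 3 RCADS points is mis-defined in the statistical section, and the progression criterion does not say whether the estimate or its confidence interval is judged

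*Protocol article*

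**What the plan says.** Three places in the protocol article bear on this point.

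- **Aims and objectives**, last feasibility question: whether the "interval estimate of benefit of IPC-A over TAU in depression scores at post-treatment include a clinically significant effect".
- **Analysis, Statistical**: "The proposed primary outcome measure for the definitive RCT is the RCADS depression score at 10 weeks". The between-group difference comes from a "general linear model including baseline RCADS depression score and treating therapist as a random effect". The 95% CI is then used to judge whether the benefit is "feasibly greater than the minimal clinically significant difference, i.e. whether or not it is included within the CI".
- **Progression criteria, Feasibility outcomes**, last of six criteria: the "mean RCADS depression scores of the IPC-A and TAU groups at 10 weeks are indicative of a clinically significant difference in depression (3 points"). No CI or adjusted estimate is mentioned.

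The trial steering committee (TSC) makes recommendations according to how far the six criteria are met. The same section says funding for the full trial will be sought if they are met. The Sample size section says that 60 will be randomised, that this number does not rest on efficacy, and that attrition of about 20% is assumed.

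**The concern.** The phrase in the Statistical section first gives a purpose: could the benefit exceed the smallest difference that matters? It then defines that purpose by a different test: does that difference lie inside the interval? Inclusion is two-sided. An interval can miss 3 because it lies wholly below 3, which is a reason for doubt, or because it lies wholly above 3, which is the best result IPC-A could have. The literal test treats both as failure.

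The progression criterion, which is what the TSC will weigh, uses the same threshold but refers to the means. Its natural reading is that the observed difference should be about 3 points or more, which is far stricter than asking whether the CI reaches 3. If the text is left as it stands, the TSC cannot tell which comparison it is weighing, and the choice could be made after the result is known.

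**Working it through.** **1. The logic, which needs no assumed figure.** Let the benefit be TAU minus IPC-A, with 95% CI from L to U.

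- Stated purpose (benefit could exceed 3), and the Aims wording (the interval contains some effect of 3 or more): met if U ≥ 3.
- Literal definition in the Statistical section: met if L ≤ 3 ≤ U.
- Point-estimate reading of the progression criterion: met if the estimate ≥ 3.

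The first two differ exactly when L > 3. With a CI of 3.5 to 9, the first is met and the second is not.

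**2. The plan's own figures.** The only precision figures given are for rates with n = 60: 1.96·√(0.2·0.8/60) = 10.1% and 1.96·√(0.5·0.5/60) = 12.7%. These match the stated ±10% and ±12.5%. No precision is given for the RCADS difference.

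**3. Inputs for the RCADS difference.** From the protocol: 60 randomised 1:1, about 20% attrition, so 60 × 0.8 = 48 analysed; threshold 3 points; 95% CI, taken as two-sided. Assumed, because the protocol gives neither: SD 5 to 7 and baseline correlation r 0.4 to 0.6. Therapist clustering is ignored; it would widen the CI.

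**4. Formulas.** SE = SD·√(1 − r²)·√(4/48); half-width h = t(0.975, 45)·SE = 2.014·SE. For a true benefit d, with the estimate taken as Normal(d, SE):

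- U ≥ 3: 1 − Φ((3 − h − d)/SE)
- L ≤ 3 ≤ U: Φ((3 + h − d)/SE) − Φ((3 − h − d)/SE)
- estimate ≥ 3: 1 − Φ((3 − d)/SE)

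**5. Results.**

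| | SD 5, r 0.6 | SD 6, r 0.5 | SD 7, r 0.4 |
|---|---|---|---|
| SE | 1.15 | 1.50 | 1.85 |
| Half-width h | 2.33 | 3.02 | 3.73 |
| True benefit 0: U ≥ 3 | 28% | 51% | 65% |
| True benefit 0: 3 inside CI | 28% | 51% | 65% |
| True benefit 0: estimate ≥ 3 | 0.5% | 2% | 5% |
| True benefit 3: U ≥ 3 | 98% | 98% | 98% |
| True benefit 3: 3 inside CI | 96% | 96% | 96% |
| True benefit 3: estimate ≥ 3 | 50% | 50% | 50% |
| True benefit 6: U ≥ 3 | >99.9% | >99.9% | >99.9% |
| True benefit 6: 3 inside CI | 28% | 51% | 65% |
| True benefit 6: estimate ≥ 3 | 99.5% | 98% | 95% |

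The inclusion test is symmetric about 3, so a true benefit of 6 passes it as often as no benefit at all. It fails on the high side once the observed benefit exceeds 3 + h, which is 5.3 to 6.7 points.

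**6. Two results under the middle case (h = 3.02).**

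- Estimate 1, CI −2.02 to 4.02: meets both CI tests, fails the point-estimate reading.
- Estimate 7, CI 3.98 to 10.02: meets the upper-limit test and the point-estimate reading, fails the literal inclusion test.

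**The case against.** The strongest reply is that the intent is plain. The Statistical section states its purpose before the loose definition, and the Aims wording already carries the upper-limit meaning. A reader might infer that the protocol holds three conflicting rules. It does not: the Aims wording agrees with the purpose in the Statistical section, and only the defining clause there departs from it.

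A reader might also infer a mechanical gate that would reject IPC-A for working too well. The text does not support that either. The Statistical section attaches no decision to its CI, and the TSC weighs the extent to which all six criteria are met. The high-side failure becomes frequent only at a benefit around twice the threshold; 6 points is 0.86 to 1.2 of the assumed SDs. At a true benefit of 3 the literal and upper-limit tests differ by about 2 percentage points.

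Third, the progression criterion may be meant to be read with the Statistical section, so that its means are the adjusted ones with their CI. Silence does not prove an unadjusted point-estimate rule, and the word indicative leaves room.

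Finally, the upper-limit test is not obviously the better progression rule. It is often met with no benefit, whereas the point-estimate reading rarely is.

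All of this bears on severity and on how firm the remedy should be. It does not remove the faulty definition, or the fact that the criterion leaves open which quantity is set against 3.

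**Conclusion.** The point holds at moderate severity. The definition in the Statistical section is wrong as written, by logic alone, because a CI wholly above 3 points fails it. The progression criterion does not say whether the estimate or a CI limit is judged, and the answer matters most for small observed benefits. With no true benefit, the CI test is met about 28% to 65% of the time, against about 0.5% to 5% for a point-estimate test. At a true benefit of exactly 3, the figures are about 98% and 50%.

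These percentages rest on the assumed SD and correlation, 48 analysed, a normal approximation and no therapist clustering. The inconsistency rests on none of them. The documents do not settle which comparison the TSC ought to use; that is a trade-off between leniency and strictness for the trial team to fix in advance.

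**What to change.** 1. **Statistical section.** Replace the defining clause with: i.e. whether the benefit-side limit of the 95% CI for the baseline-adjusted difference (TAU minus IPC-A) is at least 3 points. This matches the stated purpose and the Aims, and it fixes the sign of the benefit.
2. **Progression criterion.** Refer to that same adjusted 10-week difference and its CI, and state before data are seen whether the estimate or the CI limit is compared with 3.
3. **Interpretation.** If the CI limit is chosen, add that meeting it means only that a 3-point benefit has not been ruled out, and give the TSC the pass rate under no benefit.

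The cost is a few sentences in the protocol and the TSC criteria. No extra data, participants or analyses are needed.
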